#### **14.1.4 Evaluations on Day 2**

On Day 2, study personnel will contact subject via telephone approximately 24 hours postdose and assess:

1. interim medical/medication history;
2. AE evaluations;

#### **14.1.5 Evaluations and procedures on Days 4, 11, 18, and 25**

The following procedures will be performed on Days 4, 11, 18, and 25.

##### Prior to Study Drug Administration (Predose Procedures):

1. medication/medical history;
2. symptom directed physical examination;
3. vital signs (including temperature, respiratory rate, and supine blood pressure and pulse);
4. AE evaluations.

##### Study Drug Administration (Time Recorded)

##### Post-dose Procedures:

At 2 hours postdose ( $\pm 15$  min):

5. vital signs (including temperature, respiratory rate, and supine blood pressure and pulse);
6. AE evaluations.

#### **14.1.6 Evaluations and procedures on Days 8, 15 and 22**

The following procedures will be performed on Days 8, 15 and 22.

##### Prior to Study Drug Administration (Predose Procedures):

1. medication/medical history;
2. symptom directed physical examination;
3. vital signs (including temperature, respiratory rate, and supine blood pressure and pulse);
4. AE evaluations;
5. plasma sample for study drug concentration; [Day 15 only]
6. clinical laboratory evaluations (including Chem-20, CBC, and UA; [Appendix H](#));
7. serum sample for assessment of antibodies to ShK-186; [Day 15 only]

8. patient and Investigator global assessments of psoriasis; [Day 15 only]
9. patient quality of life assessment (DLQI); [Day 15 only]
10. patient assessment of disability (PDI); [Day 15 only]
11. %BSA, Psoriasis Area and Severity Index (PASI), and target lesion assessments; [Day 15 only]
12. whole blood collection for biomarkers: PBMCs, plasma, serum and whole blood sample for RNA (TEMPUS™). [Day 15 only]

Study Drug Administration (Time recorded)

Post-dose Procedures:

At 2 hours postdose ( $\pm 15$  min):

13. vital signs (including temperature, respiratory rate, and supine blood pressure and pulse);
14. AE evaluations;
15. whole blood collection for biomarkers: PBMCs, plasma, serum and whole blood sample for RNA (TEMPUS™). [Day 15 only]

**14.1.7 Evaluations and procedures on Day 29**

The following procedures will be performed on Day 29.

Prior to Study Drug Administration (Predose Procedures):

1. interim medication/medical history;
2. symptom directed physical examination;
3. vital signs (including temperature, respiratory rate, and supine blood pressure and pulse);
4. AE evaluations;
5. plasma sample for study drug concentration;
6. clinical laboratory evaluations (including Chem-20, CBC, and UA);
7. serum sample for assessment of antibodies to ShK-186;
8. whole blood collection for biomarkers: PBMCs, plasma, serum and whole blood sample for RNA (TEMPUS™).

Study Drug Administration (Time Recorded)

Post-Dose Procedures:

At 5 minutes post dose ( $\pm 1$  min):

9. plasma sample for study drug concentration.

At 15 minutes postdose ( $\pm 5$  min):

10. plasma sample for study drug concentration.

At 30 minutes postdose ( $\pm 5$  min):

11. plasma sample for study drug concentration.

At 1 hour postdose ( $\pm 10$  min):

12. plasma sample for study drug concentration.

At 2 hours postdose ( $\pm 15$  min):

13. vital signs (including temperature, respiratory rate, and supine blood pressure and pulse);
14. AE evaluations;
15. plasma sample for study drug concentration
16. whole blood collection for biomarkers: PBMCs, plasma, serum and whole blood sample for RNA (TEMPUSTM).

At 4 hours postdose ( $\pm 15$  min):

17. plasma sample for study drug concentration.

#### **14.1.8 Evaluations and Procedures on Day 32 and 43 Procedures**

The following procedures will be performed on Days 32 and 43:

1. interim medication/medical history;
2. symptom directed physical examination;
3. vital signs (including temperature, respiratory rate, and supine blood pressure and pulse);
4. AE evaluations;
5. patient and Investigator global assessments of psoriasis; [Day 32 only]
6. patient quality of life assessment (DLQI); [Day 32 only]
7. patient assessment of disability (PDI); [Day 32 only]
8. %BSA, Psoriasis Area and Severity Index (PASI), and target lesion assessments; [Day 32 only]
9. whole blood collection for biomarkers: PBMCs, plasma, serum and whole blood sample for RNA (TEMPUSTM);
10. skin biopsy (subjects will be instructed to abstain from the use of emollients for 24 hours prior to the scheduled biopsy/photography); [Day 32 only]
11. photographic documentation of target lesion that has been assessed throughout, biopsied lesion(s), as well as psoriasis-involved body areas. [Day 32 only]

#### **14.1.9 End of Study Evaluations and Procedures (Day 57)**

The following procedures will be performed at the End of Study visit:

1. interim medication/medical history;
2. routine physical examination (including neurologic exam);
3. vital signs (including temperature, respiratory rate, and supine blood pressure and pulse);
4. AE evaluations;
5. patient and Investigator global assessments of psoriasis;

6. patient quality of life assessment (DLQI);
7. patient assessment of disability (PDI);
8. %BSA, Psoriasis Area and Severity Index (PASI) and target lesion assessments;
9. plasma sample for study drug concentration;
10. clinical laboratory evaluations (including Chem-20, CBC, and UA);
11. whole blood collection for biomarkers: PBMCs, plasma, serum and whole blood sample for RNA (TEMPUS™);
12. photographic documentation of target lesion that has been assessed throughout, biopsied lesion(s), as well as psoriasis-involved body areas (Subjects will be instructed to abstain from the use of emollients for 24 hours prior to the scheduled photography);
13. serum sample for assessment of antibodies to ShK-186;
14. serum pregnancy test (female subjects only);

Subjects that prematurely discontinue from study should complete all assessments for the scheduled visit and all End of Study assessments.

## **14.2 Safety Evaluations**

All subjects who receive study drug will be assessed for safety. The timing of the variables is presented in [Appendix A](#) and the variables will include:

- AE evaluations (all AE evaluations will include inquiry regarding the development of numbness/tingling or other symptoms/signs of neuropathy);
- Serious Adverse Events (SAE) evaluations;
- physical examination (including neurologic exam);
- vital signs (including temperature, respiratory rate, and supine blood pressure and pulse);
- clinical laboratory evaluations (including Chem-20, CBC, and UA; [Appendix H](#));
- antibody formation to ShK-186.

### **14.2.1 Clinical Laboratory Evaluations**

Clinical laboratory evaluations (including Chem-20, CBC, and UA).

Serology for hepatitis ([see Appendix H](#)), HIV antibody, and selected drugs of abuse will be performed.

Pregnancy tests (females only) will be performed (serum and urine).

### **14.2.2 Vital Signs**

Vital signs (including temperature, respiratory rate, and supine blood pressure and pulse) will be obtained.

Supine blood pressure and pulse will be measured after the subject has been supine for at least 5 minutes.

When vital signs are scheduled at the same time as blood draws, the blood draws will be

obtained at the scheduled time point, and the vitals will be obtained as close to the scheduled time point as possible.

#### **14.2.3 AE Evaluations**

Subjects will be asked a non-leading question such as “Have there been any changes in your health status since Screening/since you were last asked?” Subjects will also be encouraged to voluntarily report AEs occurring at any other time during the study. Additionally, subjects will be specifically asked about the development of numbness/tingling or other symptoms of neuropathy.

#### **14.2.4 Physical Examinations**

A routine physical examination and symptom-directed examinations will be performed.

#### **14.2.5 Neurological Examinations**

A complete neurological examination will be performed as part of screening, baseline and end of study procedures. Additional symptom-directed exams may be performed periodically throughout the study as well as when indicated by adverse events at the discretion of the Investigator.

### **14.3 Sampling for Pharmacokinetic Analysis**

#### **14.3.1 Pharmacokinetic Sample Collection and Processing**

Samples for PK analysis of ShK-186 levels will be collected, processed, stored, and shipped according to instructions provided in a separate study manual.

#### **14.3.2 Analytical Methodology**

Plasma concentrations of ShK-186 and ShK-198 (an active metabolite of ShK-186) will be determined by Chimera Biotech using a qualified analytical procedure.

### **14.4 Sampling for Biomarker Analyses**

#### **14.4.1 Blood sample collection for biomarkers**

Blood used to generate samples of plasma and PBMCs for biochemical and cellular biomarker analyses will be collected, processed, stored and shipped according to instructions provided in a separate study manual.

#### **14.4.2 Skin biopsies for biomarker evaluation**

Skin biopsies will be performed, processed, stored and shipped according to instructions provided in a separate study manual and video.

#### **14.4.3 Photographic documentation**

A digital camera will be provided to each study site. Photographs of psoriasis-involved body areas, biopsied lesions (prior to biopsy) and target lesions for assessment will be collected. Instructions for capturing and storing images are provided in the study manual.

### **14.5 Adverse Events**

#### **14.5.1 Relationship to Study Drug**

The Investigator will make a determination of the relationship of the AE to the study drug using

a 4-category system (not related, possible, probable, definite) according to the following guidelines below:

- **NOT RELATED** = an AE that does not follow a reasonable temporal sequence from administration of the drug and that can be reasonably explained by other factors, including underlying disease, complications, concomitant drugs, or concurrent treatment;
- **POSSIBLE** = an AE that follows a reasonable temporal sequence from the administration of the drug (including the course after withdrawal of the drug) and that cannot be excluded as being possibly caused by the drug (*e.g.*, existence of similar reports attributed to the suspected drug and/or its analogues; reactions attributable to the pharmacological effect of the drug), although other factors such as underlying disease, complications, concomitant drugs, or concurrent treatment are presumable;
- **PROBABLE** = an AE that follows a reasonable temporal sequence from administration of the drug (including the course after withdrawal of the drug) and that can be excluded as being possibly caused by other factors, such as underlying disease, complications, concomitant drugs, or concurrent treatment;
- **DEFINITE** = an AE that follows a reasonable temporal sequence from administration of the drug (including the course after withdrawal of the drug), follows a known or hypothesized cause-effect relationship, and (if appropriate) satisfies the following:
  - positive results obtained in drug sensitivity tests;
  - toxic level of the drug present in blood or other body fluids.

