**Figure 1. Study schematic for each cohort.**

|             | Screening* | Biopsy Collection | Dose Administration             | Evaluations                                | Evaluation and End of Study Procedures |
|-------------|------------|-------------------|---------------------------------|--------------------------------------------|----------------------------------------|
| Days | -30 to -1  | -7 to -1          | 1, 4, 8, 11, 15, 18, 22, 25, 29 | 1, 2, 4, 8, 11, 15, 18, 22, 25, 29, 32, 43 | 57                                     |

\*Screening will occur within 30 days of the first dose (Baseline, Day 1) and prior to biopsy collection and randomization. There is no Day 0 in the schedule.

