### **6.3 Subject Withdrawal Criteria**

Subjects who meet all the inclusion criteria and have none of the exclusion criteria will be eligible to be enrolled into the study.

Subjects will be informed that they are free to withdraw from the study at any time and for any reason. The Investigator may remove a subject from the study if, in the Investigator's opinion, it is not in the best interest of the subject to continue the study. Subjects may be withdrawn if there are applicable safety or tolerability concerns on the part of the Investigator. Additionally, withdrawal of an individual subject will occur if any one of the following are met:

- Occurrence of an adverse event of Grade 3 or higher (CTCAE v4.0)
  - Grade 3 and greater laboratory abnormalities, that are
    - reproducible and sustainable (repeat laboratory test performed within 24-36 hours), and
    - clinically significant (according to the Investigator's discretion),
  - Grade 3 AEs that are clinically significant but clearly not related to study drug will be considered individually for withdrawal by the investigator, based on the clinical picture and logistical ability to manage the subject.
- Occurrence of a serious adverse event (SAE)
- Development of paresthesia/peripheral neuropathy symptoms that do not resolve prior to the next dose (at the discretion of the Investigator).

Notification of discontinuation will be made immediately to the Sponsor. In case of premature discontinuation of study participation, efforts will be made to perform all final study day assessments. The date the subject is withdrawn from the study and the reason for discontinuation will be recorded on the subject's Case Report Form (CRF). All dropouts will be followed until the resolution of all their AEs or until the unresolved AEs are judged by the Investigator to have stabilized.

Subjects that withdraw after receiving study drug will not be replaced. Subjects that withdraw prior to receiving study drug will be replaced and will receive a new study number.

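### The causality scale in Section 14.5.1 cannot rate an AE close to a dose as not related, however clear its other cause, and leaves some AEs with no category at all

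*Protocol*

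**What the plan says.** Section 14.5.1 has the Investigator rate each AE by "a 4-category system (not related, possible, probable, definite) according to the following guidelines below". The four definitions are:

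- NOT RELATED is defined as "an AE that does not follow a reasonable temporal sequence from administration of the drug and that can be reasonably explained by other factors".
- POSSIBLE: a reasonable temporal sequence, "and that cannot be excluded as being possibly caused by the drug", with the concession "although other factors such as underlying disease, complications, concomitant drugs, or concurrent treatment are presumable".
- PROBABLE: a reasonable temporal sequence, "and that can be excluded as being possibly caused by other factors, such as underlying disease, complications, concomitant drugs, or concurrent treatment".
- DEFINITE: a reasonable temporal sequence, and the event "follows a known or hypothesized cause-effect relationship, and (if appropriate) satisfies the following", after which two laboratory-type criteria are listed.

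There is no category for unlikely or unassessable events, and no time window is attached to the temporal condition.

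Section 6.3, and the matching text under Subject Withdrawal Criteria in the Synopsis, sets apart "Grade 3 AEs that are clinically significant but clearly not related to study drug", which the investigator is to consider individually for withdrawal.

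**The concern.** A causality scale should give every AE a place. Here the two reasons for calling an event unrelated (wrong timing, or another cause) are joined by *and*, so neither is enough alone. Since the other three categories all need a temporal link, an event that misses NOT RELATED may have nowhere to go.

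Such events are to be expected. Section 14.5.2 counts accidents and concomitant diseases as AEs. Section 3.3 reports a withdrawal for viral gastroenteritis in the earlier study of nine twice-weekly doses. Sections 14.1.2 and 14.1.8 place skin biopsies in the week before the first dose and on Day 32, nominally three days after the last dose. Biopsy-site events can therefore lie close to a dose and still be plainly procedural.

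Safety is the primary objective (Section 4.1). When the definitions do not fit the event, raters must improvise, and up to 4 centers (Section 5.1.1) may improvise differently. For non-serious AEs, the Investigator's rating is the only causality assessment that the protocol describes.

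**Working it through.** **Inputs.** The four definitions (Section 14.5.1), the withdrawal wording (Section 6.3), the dosing days "1, 4, 8, 11, 15, 18, 22, 25, 29" (Figure 1), and 24 subjects at 5:5:2 (Section 5.1). The plan states no figure on this point, so there is none to reproduce.

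**Step 1: try each kind of event against the literal definitions.**

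| Temporal sequence? | Other cause | Drug cause | Cause-effect relationship hypothesized? | Category that fits |
|---|---|---|---|---|
| No | Explains the AE | Either | Either | NOT RELATED |
| No | No explanation | Either | Either | None |
| Yes | Explains the AE | Can be excluded | No | None |
| Yes | Presumable | Cannot be excluded | No | POSSIBLE |
| Yes | Excluded | Either | No | PROBABLE |

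Rows 2 and 3 are the gaps. Row 3 is the accident, infection or biopsy-site event soon after a dose. It fails NOT RELATED on timing, POSSIBLE because the drug can be excluded, PROBABLE because another cause is present, and DEFINITE because no cause-effect relationship applies.

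**Step 2: set this beside Section 6.3.** That clause presupposes that an AE can be clearly not related. Under Section 14.5.1 a clear other cause does not earn that rating if the event is close to a dose. The two passages need to be reconciled. This is a matter of definition and takes no position on the withdrawal rule itself.

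**Step 3: how much dosing time is affected?** The gaps between doses are 3, 4, 3, 4, 3, 4, 3 and 4 days, which sum to 28. For an assumed window of *w* days after each dose, the share of Days 1 to 29 inside the window is the sum of min(*w*, gap) over the eight gaps, divided by 28:

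- 12 h: 8 × 0.5 = 4; 4/28 = 14%
- 24 h: 8 × 1 = 8; 8/28 = 29%
- 48 h: 8 × 2 = 16; 16/28 = 57%
- 72 h: 8 × 3 = 24; 24/28 = 86%
- 96 h: 4 × 3 + 4 × 4 = 28; 28/28 = 100%

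These are shares of time. They equal shares of AEs only if onsets are spread evenly.

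**Step 4: what one rating is worth.** 24 × 5/12 = 10 subjects per active arm and 24 × 2/12 = 4 on placebo. Moving one subject between related and not related changes an arm's related-AE incidence by 1/10 = 10 percentage points (active) or 1/4 = 25 points (placebo).

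**The case against.** The definitions are offered as guidelines, and an experienced Investigator will rate an obvious accident as not related whatever the conjunction says. All AEs are recorded regardless of causality (Section 14.5.2), safety is summarized descriptively (Section 9.1), and no related-AE endpoint is named. All SAEs are reported whether related or not, and the sponsor assesses their relatedness separately (Section 14.5.3). The Investigator is blinded (Section 7.4), so loose rating is not shown to favor an arm. Section 6.3 does not cite the Section 14.5.1 categories.

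Most of this stands, and it limits the consequence. It does not remove the defect: guidelines that must be disregarded to reach the sensible answer are badly drafted, and the SAE safeguards do not reach non-serious AEs.

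Two stronger readings are tempting, and the documents support neither.

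- A reader might infer that under twice-weekly dosing almost no on-treatment AE could be NOT RELATED. That needs a window of about 72 to 96 h. The protocol sets none, and the one time course it reports for a drug effect is paresthesia that usually resolved within 12 hours (Section 3.3). That figure describes paresthesia only and does not fix a window for other events.
- A reader might infer that events clearly due to another cause drop into POSSIBLE and inflate related AEs in every arm. POSSIBLE also requires that drug cause cannot be excluded, so such an event has no category. No direction of bias follows.

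**Conclusion.** The concern holds as a drafting defect with two gaps: AEs close to a dose with a clear other cause, and AEs with neither a temporal link nor another explanation. Both follow from the wording alone, and the first conflicts with the withdrawal criteria.

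How often the first gap arises cannot be determined, because it depends on what raters accept as a reasonable temporal sequence. The 14% to 100% range is conditional on assumed windows of 12 to 96 h and is not an estimate of misclassified events. The 10- and 25-point shifts show how sensitive arms of this size are to one rating; they do not predict a bias. Given the safeguards for SAEs, this is a minor point worth correcting because safety is the primary objective and the correction is nearly free.

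**What to change.** Reword NOT RELATED along these lines: *there is no reasonable temporal sequence from dosing, OR the event is clearly explained by other factors such that drug cause can be excluded*. Keep POSSIBLE for temporally plausible events where drug cause cannot be excluded. Then reconcile the wording with the withdrawal criteria in the Synopsis and Section 6.3, so that the term means the same thing in each place.

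There is one small downside: an unexplained AE without a temporal link would now be rated NOT RELATED. Because immunogenicity is part of the primary objective, the CRF instruction should say that delayed effects such as immune reactions can still count as following a reasonable temporal sequence.

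The cost is one reworded definition, a cross-check of two passages and a matching CRF instruction. No extra data are collected.

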#### 14.5.2 Recording Adverse Events

An AE is defined as any untoward medical occurrence experienced by a patient or healthy subject, whether or not considered drug related by the Investigator. A treatment emergent AE is an AE that is reported after a dose of study drug.

Adverse events/experiences are all:

- unfavorable changes in general condition;
- subjective or objective signs/symptoms;
- concomitant diseases or accidents;
- clinically relevant adverse changes in laboratory parameters observed in a subject in the course of a clinical study.

Adverse events/experiences comprise all disturbances of general health status, subjective and objective disease symptoms (including laboratory abnormalities), and accidents observed in the context of a clinical trial, irrespective of a possible causal relationship with the administration of the trial substance. Events occurring in the framework of a clinical trial during drug-free, and post-study drug periods, under placebo, or in a reference group receiving drug or non-drug therapy, are also to be designated as AEs.

All AEs, whether volunteered, elicited, or noted on physical examination, will be recorded throughout the study (*i.e.*, from the time of first injection on Day 1 until End of Study).

The severity of AEs that are clinical abnormalities, vital signs, and systemic issues will be

categorized according to the criteria presented in the Common Terminology Criteria for Adverse Events v4.0.

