### **7.2 Concomitant Medications**

Excluded systemic medications should be discontinued at least four weeks prior to baseline or five half-lives, whichever is longer.

Topical medications should be discontinued at least two weeks prior to baseline.

Subjects will refrain from participation in another clinical trial with receipt of an investigational product within 90 days of baseline (or 5 half-lives of the previous drug, whichever is longer).

Other agents for the treatment of psoriasis should not be added without prior approval of the Investigator.

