#### **14.1.2 Biopsy Procedures (Pre-dose, Day -7 to -1)**

Within one week of the first dose of study drug, subjects will present to the clinic to obtain a 6 mm punch biopsy of a psoriatic plaque (not the target lesion for assessment), as well as one 6 mm punch biopsy of healthy adjacent skin (at least 2.5 cm away from the lesion). Alternatively, two 4 mm biopsies may be collected if a single 6 mm biopsy cannot be obtained or if subject tolerability would be improved, as judged by the Investigator. Subjects will be instructed to abstain from the use of emollients for 24 hours prior to the scheduled biopsy/photography. Subject eligibility will be reviewed and randomization will occur prior to collection of biopsy tissue.

A target lesion for continued on-study assessment will be identified. Photographic documentation of the target lesion, biopsied lesion(s), location of healthy adjacent skin biopsy and psoriasis-involved body areas will be collected according to procedures described in the study manual.

Whole blood will be collected for biomarker analysis.

Subjects will be randomized.

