#### **14.1.3 Baseline (Day 1, First-Dose) Procedures**

On Day 1, subjects will report to the study site and the following procedures will be performed.

Prior to Study Drug Administration (Predose Procedures):

1. interim medical and medication history;
2. routine physical examination (including neurologic exam);

3. weight;
4. vital signs (including temperature, respiratory rate, and supine blood pressure and pulse);
5. Review of subject eligibility
6. patient and Investigator global assessments of psoriasis§;
7. patient quality of life assessment (DLQI)§;
8. patient assessment of disability (using PDI)§;
9. %BSA involved and PASI§;
10. non-biopsied target lesion assessment§;
11. whole blood collection for biomarkers: PBMCs, plasma, serum and whole blood sample for RNA (TEMPUS TM);
12. clinical laboratory evaluations (including Chem-20 [fasted at least 4 hours], CBC, and UA);
13. baseline plasma sample for study drug concentration;
14. serum sample for assessment of antibodies to ShK-186;
15. urine pregnancy test (for females only); for female subjects to continue their participation in the study, the pregnancy test must be negative.

Study Drug Administration:

16. study drug will be administered and the start time of study drug administration will be recorded. Postdose study procedures will be based on study drug administration time.

Post-dose Procedures:

At 5 minutes post dose ( $\pm 1$  min):

17. plasma sample for study drug concentration.

At 15 minutes postdose ( $\pm 5$  min):

18. plasma sample for study drug concentration.

At 30 minutes postdose ( $\pm 5$  min):

19. vital signs (including temperature, respiratory rate, and supine blood pressure and pulse);
20. AE evaluations;
21. plasma sample for study drug concentration.

At 1 hour postdose ( $\pm 10$  min):

22. plasma sample for study drug concentration.

At 2 hours postdose ( $\pm 15$  min):

23. vital signs (including temperature, respiratory rate, and supine blood pressure and pulse);

---

§ Evaluation can be performed during the biopsy collection visit at Investigator's discretion.

24. AE evaluations;
25. plasma sample for study drug concentration;
26. whole blood collection for biomarkers: PBMCs, plasma, serum and whole blood sample for RNA (TEMPUS™).

At 4 hours postdose ( $\pm 15$  min):

27. plasma sample for study drug concentration.

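### Treatment-emergent AEs are defined by time of report, and no AE question precedes the first dose, so pre-dose biopsy and washout complaints can be counted as treatment-emergent

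*Protocol*

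**What the plan says.** Section 14.5.2 of the protocol makes three statements that bear on this point.

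- The definition: "A treatment emergent AE is an AE that is reported after a dose of study drug".
- The recording window: AEs are recorded "from the time of first injection on Day 1 until End of Study".
- The scope of the term AE: "Events occurring in the framework of a clinical trial during drug-free, and post-study drug periods" are also to be designated AEs.

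Section 14.2.3 gives an example of the AE question: "Have there been any changes in your health status since Screening/since you were last asked". It is offered as an illustration, and its two alternatives give two look-back periods.

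In section 14.1.3 the fifteen numbered Day 1 items before dosing include no AE evaluation. The first is "20. AE evaluations", listed at 30 minutes after the dose, and the second follows at 2 hours. Appendix A agrees: the pre-dose AE row is blank for Screening, Pre-dose and Baseline, and Day 1 shows two AE evaluations, both in the post-dose block.

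Two sources of complaints precede the first dose.

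- Biopsy (section 14.1.2): "Within one week of the first dose of study drug, subjects will present to the clinic to obtain a 6 mm punch biopsy", with a further biopsy of healthy skin. The order is fixed: "Subject eligibility will be reviewed and randomization will occur prior to collection of biopsy tissue".
- Washout (section 7.2): "Excluded systemic medications should be discontinued at least four weeks prior to baseline or five half-lives, whichever is longer". Topical treatments stop at least two weeks before baseline.

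**The concern.** A treatment-emergent label exists to separate what began or worsened on study drug from what was already there. A rule based on the date of report cannot do that. It classifies by when someone happened to mention an event, and here the first scheduled occasion to mention one as an AE comes after the first injection.

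Safety and tolerability are part of the primary objective (section 4.1). The pre-dose period is not quiet. Subjects stop their psoriasis treatments, and within the last week they have at least two punch biopsies, one lesional and one of healthy skin. Soreness at a biopsy site or a flare off treatment is an ordinary thing to report when asked about changes in health. If such complaints enter the treatment-emergent counts, they raise the background in all three groups and make drug and placebo look more alike.

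**Working it through.** The protocol gives no figure to reproduce here. The check is of text and schedule, with a little arithmetic.

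**Step 1. Does the label separate anything?** Recording starts at the first injection, and treatment-emergent means reported after a dose. Any AE in the record was therefore reported after a dose, and the set of treatment-emergent AEs equals the set of recorded AEs. This holds whether the recording window is read as limiting the date of report or the date of onset.

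**Step 2. Can a pre-dose event enter the record?** The two readings of the window differ.

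- Window read as date of report: an event with onset on Day -3, first mentioned 30 minutes after the dose, is recorded and is treatment-emergent.
- Window read as date of onset: the same event is not recorded as an AE. That reading sits badly with the sentence in the same section that treats events in drug-free periods as AEs.

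The text does not choose between them.

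**Step 3. How many AE evaluations precede the first dose?** None in sections 14.1.1 or 14.1.2, none in 14.1.3 items 1 to 15, and none in Appendix A. On every later dosing day (sections 14.1.5 to 14.1.7) an AE evaluation does precede the dose. Day 1 is the exception, and it is the day that sets the baseline.

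**Step 4. How much of the first look-back is on drug?** If the 30-minute question reaches back to Screening *d* days earlier, the post-dose share is 0.5 h / (24 h × *d* + 0.5 h).

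| Days since Screening | Post-dose share |
|---|---|
| 30 (longest allowed) | 0.5 / 720.5 = 0.07% |
| 7 | 0.5 / 168.5 = 0.30% |
| 1 | 0.5 / 24.5 = 2.0% |

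On that reading almost all of the period asked about precedes the drug. On the other alternative, since last asked, the period could be much shorter.

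**Step 5. What would it do to the comparison?** Randomising 24 subjects 5:5:2 gives 10, 10 and 4. One subject with no other treatment-emergent event who is wrongly counted moves incidence by 1/10 = 10 points in an active arm and 1/4 = 25 points on placebo. These steps show how coarse the arms are. They do not measure this defect.

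Let *q* be the risk that a subject has a pre-dose event counted this way, the same in each arm and independent of true events. The observed risk is 1 − (1 − *p*)(1 − *q*), so a true difference is multiplied by (1 − *q*). The following inputs are assumptions, not document figures: true risks of 20% on placebo and 90% on active, with *q* from 10% to 50%.

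- *q* = 10%: 28% against 91%, a difference of 63 points instead of 70.
- *q* = 50%: 60% against 95%, a difference of 35 points instead of 70.

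This shows direction and mechanism only.

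**The case against.** **Pre-dose information is collected.** Before the Day 1 dose, section 14.1.3 requires an interim medical and medication history, a physical and neurologic examination and a review of eligibility. Disease activity is scored before dosing too, so a washout flare has a baseline. This stands in part. A reader might infer that pre-dose events go unrecorded, and the documents do not support that. What is missing is a sentence saying that events found at this history are baseline conditions and not treatment-emergent.

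**The window may be an onset limit, and the question has a second alternative.** Both are fair. A reader might infer that every pre-dose complaint is treatment-emergent by rule. The text supports only that such complaints can be.

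**The numbness and tingling inquiry.** Because this is asked at each AE evaluation, a reader might infer that it suffers in particular. The documents do not support that. Section 6.2 excludes present or past paresthesia or neuropathy and an abnormal neurologic examination, and eligibility is reviewed again on Day 1. Section 3.3 places the known effect around the mouth, hands and feet, while section 6.1 bars plaques on the face, palms and soles from biopsy. Local numbness at a biopsy site can be told apart.

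**The label drives no stated analysis.** Section 9.1 summarises adverse events descriptively, and the term occurs only in section 14.5.2. A statistical analysis plan, not shown, might redefine it. That is possible, but the protocol does state a definition, and no later plan can supply a pre-dose AE inquiry that was never made.

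**The error does not depend on arm.** Correct in expectation: these events precede any drug, and treatment is blinded. The consequence is dilution and chance imbalance, not systematic bias towards one arm.

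**Conclusion.** The definition is wrongly stated. It rests on the time of report, has no onset or worsening criterion, and with the recording window it labels every recorded AE as treatment-emergent. Since the first AE evaluation follows the first dose and may look back to Screening, biopsy-site and washout complaints with earlier onset can be counted. This bears on the primary objective.

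The effect is added background and a diluted active-placebo contrast, with chance imbalance mattering because only 4 subjects receive placebo. The conclusion rests on the wording and the schedule, not on an assumed event rate. A reader might want the number of subjects affected, but the protocol gives no rate of pre-dose complaints and no indication of how many would bypass the Day 1 history, so any such number would be a guess. The point concerns the pre-dose biopsy only: events from the Day 32 biopsy begin after dosing and are treatment-emergent by onset as well.

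**What to change.** 1. In section 14.5.2, define a treatment-emergent AE as an AE with onset, or worsening in severity, at or after the first dose on Day 1 through End of Study.
2. Add an AE inquiry to the Day 1 pre-dose list in section 14.1.3 and to the Baseline column of the pre-dose AE row in Appendix A. List events with pre-dose onset, including those from the pre-dose biopsy after randomisation, separately from treatment-emergent AEs. Align the recording-window sentence in section 14.5.2 so that it admits these events, and state that those found at the Day 1 pre-dose history are handled in the same way.

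The cost is a few sentences, one question at a visit already held, and a few more AE lines to record and code. The change should be in place before the first subject is dosed, because a pre-dose AE inquiry that was not made cannot be fully reconstructed afterwards.
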